## Abstract

**Background:**

Acute pharyngitis accounts for an estimated 15 million patient visits in the United States. However, there is no proven effective and safe treatment. Although Chinese herbal medicine is widely used in the treatment of acute pharyngitis, there is a lack of evidence-based data. Despite several clinical trials conducted in this setting, no randomized placebo-controlled trial has been performed to date. This trial aims to investigate the efficacy and safety of Qi-Wei-Qing-Yan aerosol (QWQYA), a Chinese herbal prescription, compared with a placebo aerosol in the treatment of acute pharyngitis with lung-stomach excess-heat syndrome.

**Methods/design:**

This is a prospective, multicenter, randomized, double-blinded, parallel-group, placebo-controlled trial. A total of 420 adult patients, of either sex, with acute pharyngitis will be enrolled from seven study sites across China. All patients will be randomly allocated to one of three parallel treatment groups: (1) QWQYA with the current propellant, (2) QWQYA with a previous propellant, and (3) the placebo aerosol with the current propellant. The study medication will be administered into the pharyngeal region in three sprays thrice daily for 5 consecutive days. The primary outcome measures are time to complete resolution of sore throat and relief rate of sore throat. Secondary outcome measures include resolution rate of sore throat, time to relief of sore throat, intensity of sore throat, and change of traditional Chinese medicine syndrome score and clinical signs score from baseline to post-treatment, as well as the occurrence of any adverse events.

**Discussion:**

This will be the first clinical trial to investigate the efficacy and safety of QWQYA in the treatment of acute pharyngitis in an adult population in a multicenter, randomized, double-blinded, parallel-group, placebo-controlled manner. Not only might it establish the basis for the efficacy and safety of QWQYA in treating acute pharyngitis, but it might also provide evidence to support the use of Chinese herbal medicine in treating acute pharyngitis and thus support an alternative treatment option for management of acute pharyngitis.

**Trial registration:**

Chinese Clinical Trial Registry ChiCTR-IPR-15005991.

## Background

Acute pharyngitis is characterized by an inflammation of mucous membranes of the pharynx and the surrounding lymphoid tissue and accounts for an estimated 15 million patient visits in 2006 in the United States [1]. It is commonly caused by various viral or bacterial infections. Viruses are the most common cause, accounting for up to 40 % to 60 % of cases [2]. The most common type of bacterial infection is group A beta-hemolytic streptococcal (GABHS) infection, which is responsible for around one-third of pediatric pharyngitis but only 5 % to 10 % of adult pharyngitis [3, 4]. An acute onset of sore throat is the predominant symptom, accounting for more than 10 % of all primary care visits [1].

Antibiotics are indicated to prevent suppurative complications and rheumatic fever, and decrease infectivity, but may only provide limited benefit in the resolution of symptoms, shortening sore throat duration by less than 1 day [5]. Moreover, excessive or inappropriate use of antibiotics may be associated with the potential side effects, increased antibacterial drug resistance, and high medical costs [6, 7]. Given that the majority of cases are caused by viral pathogens, the current treatment strategy in adults focuses on the relief of symptoms, particularly sore throat. Corticosteroids may reduce the severity and duration of pain, but corticosteroids alone should not be administered as routine treatment, owing to potential side effects [8–10]. Nonsteroidal anti-inflammatory drugs can reduce sore throat pain in 24 hours but are associated with gastrointestinal, renal, or hepatic adverse effects [11]. Although gargles or lozenges with local anaesthetic also provide sore throat pain relief, the effect is short-lived or temporary [3, 12].

Owing to a lack of proven effective and safe therapies in Western medicine, an increasing number of patients turn to complementary and alternative medicine [13–15], including traditional Chinese medicine, for relief of symptoms of acute pharyngitis. In traditional Chinese medicinal theory, acute pharyngitis falls into the disease category of pharyngitis (houbi in Chinese Pinyin), and is mainly caused by external causes, including wind and heat. Based on traditional Chinese medicinal clinical practice, wind-heat syndrome and lung-stomach excess-heat syndrome are the most common syndromes. Of these, lung-stomach excess-heat syndrome is more common in patients, with underlying heat in the lungs and stomach, and is primarily characterized by sore throat, cough, dryness of throat, thirst, and fever. The general traditional Chinese medicinal therapeutic principle is to clear away heat and toxins, and to relieve the sore throat.

Although traditional Chinese medicine has been widely used in China for the treatment of acute pharyngitis for thousands of years, Chinese herbal medicine is not recommended for use as an effective therapy, owing to the lack of high-quality clinical trials in this area [16]. Qi-Wei-Qing-Yan aerosol (QWQYA) is a registered herbal prescription in China and manufactured by Shandong Bencao Pharmaceutical Co., Ltd (Shandong, China). Table 1 lists the detailed formula. Despite the use of QWQYA in acute pharyngitis for several years, its efficacy has never been investigated through a placebo-controlled trial. Moreover, dichlorodifluoromethane (CFC-12), the previous propellant of QWQYA, has gradually been banned by the Ministry of Environmental Protection of the People’s Republic of China, owing to its ozone-depleting properties [17]. Alternatively, 1,1,1,2-tetrafluoroethane (HFC-134a) is used as the current aerosol propellant, owing to its negligible ozone depletion potential [18]. Accordingly, the safety of QWQYA with the current aerosol propellant remains unknown.

**Table 1 Tab1:** Formula of Qi-Wei-Qing-Yan aerosol

Pinyin name	Botanical or zoological authority	Family name
Shandougen	*Euchresta japonica Hook. f. ex Regel*	Leguminosae
Shegan	*Belamcanda chinensis (L.) Redouté*	Iridaceae
Xuanshen	*Scrophularia ningpoensis Hemsl.*	Scrophulariaceae
Maidong	*Ophiopogon japonicus (L. f.) Ker-Gawl.*	Liliaceae
Chansu	*Bufo bufo gargarizans Cantor*	Bufonidae
Rengong Shexiang	*Moschus (Artificial)*	Not applicable
Bingpian	*Dryobalanops aromatica Gaertn.f.*	Dipterocarpaceae

The objective of this trial is to evaluate the efficacy and safety of two QWQYAs (active medication with the current or previous propellant) in comparison with a placebo aerosol (placebo with the current propellant) in patients with acute pharyngitis (lung-stomach excess-heat syndrome). In this study, the investigators hypothesize that (1) time to complete resolution of sore throat will be shorter in the groups using QWQYA with the current or previous propellant; (2) the proportion of patients who achieve sore throat pain relief will be higher in the groups using QWQYAs; and (3) QWQYA with the current propellant will be safe.

## Methods/design

This is a prospective, multicenter, randomized, double-blinded, parallel-group, placebo-controlled trial of two QWQYAs (active medication with the current or previous propellant) versus placebo aerosol (placebo with the current propellant) for acute pharyngitis. The study has been authorized by the China State Food and Drug Administration (Approval No. 2014 L00188). In addition, the study was registered with the Chinese Clinical Trial Registry (ChiCTR-IPR-15005991). The trial protocol is conducted in accordance with the Declaration of Helsinki, the code of Good Clinical Practice, and the guidelines of the International Conference on Harmonisation. Recruitment is scheduled to occur from early April 2015 until October 2015. Figure 1 shows the flow chart of the trial.

**Fig. 1 Fig1:**
[figure not shown]
Study flow chart. *QWQYA* Qi-Wei-Qing-Yan aerosol

### Patient population and setting

The diagnosis is made by medically qualified physician based on the presence of acute onset symptoms and signs suggestive of acute pharyngitis [19]. All patients will be screened for Centor criteria (history of fever (>38 °C), tonsillar exudates, tender anterior cervical adenopathy, and lack of cough) to focus on viral acute pharyngitis. Adults with none or only one of these findings will be included. Traditional Chinese medicinal diagnosis of lung-stomach excess-heat syndrome is based on the Guidelines for Clinical Research of New Chinese Medicine [20]; detailed criteria are presented in Table 2.

**Table 2 Tab2:** Traditional Chinese medicine syndrome diagnostic criteria for lung-stomach excess-heat syndrome

Category	Symptoms or signs
Main symptom	Sore throat
Minor symptoms	Cough, dryness of throat, thirst, fever, dry stool, deep-colored urine
Tongue appearance	Light red appearance
Tongue coating	Thin yellow coating
Pulse	Rapid and powerful pulse

The syndrome can be diagnosed by the presence of the main symptom and ≥3 minor symptoms.

A written, signed, and dated informed consent form should be obtained from each patient before any study specific procedures are performed. The participant information sheet and informed consent form will be presented to patients by the responsible clinician, who will explain the exact nature of the study, the implications and constraints of the protocol, the known side effects, and any benefits or risks involved in participation, and the importance of completing the study. It is clearly stated that the participant is free to withdraw from the study at any time for any reason without prejudice to future care, and with no obligation to give the reason for withdrawal.

A total of 420 patients of either sex, aged 18–65 years, will be enrolled from seven study sites across China: (1) West China Hospital of Sichuan University, (2) Xiyuan Hospital of China Academy of Chinese Medical Sciences, (3) the first Affiliated Hospital of Guiyang College of Traditional Chinese Medicine, (4) Ruikang Hospital Affiliated to Guangxi University of Chinese Medicine, (5) the Affiliated Hospital of Shanghai University of Traditional Chinese Medicine, (6) the Affiliated Hospital to Liaoning University of Traditional Chinese Medicine, and (7) the Affiliated Hospital of Chengdu University of Traditional Chinese Medicine. A research assistant in each center will recruit patients either from outpatient departments, or through advertisements in community hospitals or pharmacies. Each participating center will recruit 60 patients.

#### Inclusion criteria

Clinical diagnosis of acute pharyngitis;Lung-stomach excess-heat syndrome in traditional Chinese medicine;Within 48 hours of onset;Centor criteria ≤1;Baseline sore throat score by visual analog scale of 5 or more, and by traditional Chinese medicine score of 6 or more;Aged 18 to 65 years;Patient must voluntarily give written, informed consent and report adverse events and concomitant medication for duration of study.

#### Exclusion criteria

Patients with temperature greater than 38.5 °C;Use of any medication taken for relief of sore throat prior to study initiation;Current use of analgesic or anti-inflammatory regimen, such as analgesics, nonsteroidal anti-inflammatory drugs, or steroids;Chronic pharyngitis;Patients with any suspected or known heart disease;Sore throat caused by local irritation of mucous membranes due to gastroesophageal reflux or ingestion of caustic substances;Patient with severe primary disease of pulmonary, hepatic, renal, or hematological system, or other serious diseases affecting survival, such as cancer or AIDS;Abnormal results to myocardial markers test, electrocardiogram abnormality, alanine transaminase or aspartate aminotransferase > 1.5 times of normal upper limit, abnormality of serum creatine, white blood cell count < 3 × 10^9^/l or >10 × 10^9^/l, and neutrophil granulocyte >80 %;Pregnancy or potential pregnancy or lactation; Allergic constitution or known allergy to any component in QWQYA; Patients taking similar medicines in the previous month or having participated or participating in other trials in previous 3 months; Mentally or legally disabled patients.

### Withdrawal criteria

Once randomly allocated to a group, a patient will be regarded as included in the study. However, patients may voluntarily withdraw from the study at any time for lack of efficacy, worsening condition, or any other reason. Researchers can withdraw patients from the trial owing to patients’ lost to follow-up, development of allergic reaction, serious adverse events, condition apparently worsening, use of forbidden medications or treatments, unblinding, or actual usage of trial medication of <80 % or >120 % of the required dosage. Withdrawn patients will not be replaced. Any participant will be perceived as having completed the study if all post-treatment assessments have been performed.

### Termination criteria

The entire study will be terminated prematurely or suspended by the investigators in the case of serious adverse events, poor efficacy observed during the study, or significant deviation from the protocol, by the National Pharmaceutical Supervisory and Administrative Department for any reason, or by the sponsor due to management or funding problems.

### Randomization and blinding

Stratified blocked randomization will be applied in the study. Randomization sequence is generated in blocks of seven in a 1:1:1 ratio by an independent statistician not involved with the participants’ enrollment or study analysis, using Statistical Analysis System SAS (SAS 9.3). The random treatment assignment for each patient will be concealed and stored in advance in two opaque, sealed, sequentially numbered envelopes. Each set of envelopes corresponds to a unique allocation code containing the specified treatment group. The sealed envelopes are kept in a fireproof place, and will only be opened in case of a medical emergency. Participants, investigators, coordinators together with statisticians are all blinded to group assignments throughout the study.

### Investigational medicinal product

Both QWQYAs contain 6.2 g/7 ml of the active solution with the excipients of ethanol, propylene glycol, and span-80 (one with the current propellant and the other with the previous propellant). Placebo aerosol with the current propellant contains 0.31 g/7 ml of placebo solution with the same excipients for appropriate blinding. Each spray equals 32.6 mg/0.037 ml of active solution and 1.6 mg/0.037 ml of placebo solution.

Both active and placebo aerosols are manufactured by Shandong Bencao Pharmaceutical Co., Ltd., in accordance with the principles of Good Manufacturing Practice. Medication supplies are coded, packed, and labelled in a blinding manner according to the randomization list. Each investigational medicinal product package contains an aerosol. Both active and placebo aerosols are issued in bottles identical in shape, size, and color. A clearly visible label on each package states ‘FOR TRIAL USE ONLY’ and other information, including function and indication, name, dose, dosing schedule, storage condition, expiry date, and the manufacturer’s name. An independent drug administrator in each center is responsible for receipt, handling, storage, dispensing, and retrieval of all investigational medicinal products. The standard operating procedures, and the manner in which the records are kept, must be documented. An overview of consent, screening, enrollment, intervention, timing of measurements, and data collection is shown in Fig. 2.

**Fig. 2 Fig2:**
[figure not shown]
Schedule of study procedures. Participants will receive the study medication for 5 days after enrollment and allocation. The time-points of assessments are shown in the schedule. QWQYA, Qi-Wei-Qing-Yan Aerosol; TCM, traditional Chinese medicine; VAS, visual analog scale

### Interventions

All participants are randomly allocated to one of three parallel treatment groups: (1) QWQYA with the current propellant, three sprays into the pharyngeal region thrice daily; (2) QWQYA with the previous propellant, three sprays into the pharyngeal region thrice daily; and (3) the placebo aerosol, three sprays into the pharyngeal region thrice daily. The scheduled treatment duration will be 5 consecutive days.

### Concomitant treatments and forbidden medication

Patients can take any Western medication or other Chinese herbal medicine that may relieve sore throat or other symptoms of acute pharyngitis, or use antibiotics and anti-viral agents during the study, but then they will be withdrawn from the study. Medications used to control underlying conditions, such as hypertension or diabetic mellitus, are allowed. Any concomitant treatment or medication administered must be recorded carefully in case report forms, including the name, dose, dosing schedule, mode of administration, and treatment period.

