### Outcome measures

#### Primary outcome measures

Time to complete resolution of sore throat, i.e., length of time from the start of treatment until complete resolution. Sore throat will be assessed using an 11-point (0 to 10) numeric visual analog scale, with 0 indicating ‘no pain’ and 10 indicating ‘worst possible pain’. This score will be evaluated thrice daily, immediately before spraying. Complete resolution of sore throat is defined as a reduction of the score to 1 or less, lasting for more than 24 hours [21].Relief rate of sore throat: this is defined as a reduction by 50 % in the baseline visual analog scale score recorded prior to treatment (day 0), lasting for more than 24 hours. The relief rate of sore throat is the proportion of patients who achieve relief of sore throat.

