### Statistical analysis

An independent statistician will perform statistical analysis using SAS 9.3. The full analysis set population includes all randomized participants as allocated. Only missing data regarding the primary outcomes will be adjusted using the last observation carried forward method. The per-protocol population includes only patients who fulfil the protocol. Analysis of efficacy will be performed based on the full analysis set and per-protocol population. Safety analyses will be performed in those populations, which include all randomized participants who receive at least one spray of medication and who have at least one visit for safety, whether or not they are withdrawn prematurely.

A fully specified statistical analysis plan will be written before unmasking. Quantitative variables will be described as mean ± standard deviation or median, and qualitative variables as frequency and percentage. Baseline analyses will be performed using analysis of variance (ANOVA) or rank-sum test for quantitative data and chi-squared or Fisher’s exact test for qualitative data. A non-inferiority test will be used to compare the two active QWQYA groups, and a superiority test to compare the current-propellant QWQYA group and the placebo group. A one-sided confidence interval method will be used in efficacy analyses. Statistical significance will be considered for *P* ≤ 0.05.

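### Withdrawing users of other medicine and filling their scores by LOCF can credit a lasting relief or resolution that nobody observed

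*Protocol article*

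**What the plan says.** All references are to the Protocol article.

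- **Concomitant treatments and forbidden medication:** patients may take Western or other Chinese medicine for sore throat or other symptoms of pharyngitis, "or use antibiotics and anti-viral agents during the study, but then they will be withdrawn from the study". Withdrawal criteria also lists "use of forbidden medications or treatments" as a reason for which researchers can withdraw a patient. Withdrawn patients are not replaced.
- **Statistical analysis, population:** "The full analysis set population includes all randomized participants as allocated". Withdrawn patients therefore stay in the full set.
- **Statistical analysis, missing data:** "Only missing data regarding the primary outcomes will be adjusted using the last observation carried forward method". No exception is made for patients withdrawn after other medicine.
- **Primary outcome measures:** complete resolution is "a reduction of the score to 1 or less, lasting for more than 24 hours". Relief is a 50% fall from baseline that lasts equally long. On the timing of scores: "This score will be evaluated thrice daily, immediately before spraying".
- **Inclusion criteria:** "Baseline sore throat score by visual analog scale of 5 or more".
- **Statistical analysis, comparisons:** "A non-inferiority test will be used to compare the two active QWQYA groups". The current-propellant aerosol is tested for superiority over placebo.
- **Data management, monitoring, and auditing:** efforts will be made to obtain consent for outcome collection when medication is discontinued. No rule says that diary scoring continues, or how such scores would be used.

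**The concern.** Each rule is common enough alone; the trouble lies in the combination. Both primary outcomes depend on duration. Withdrawal from the study, rather than from study medication, ends the observation that could confirm or refute that duration. LOCF then fills the gap with one constant value. If the last score before withdrawal happens to be low, the filled series shows a low score for the rest of the five days and meets the 24-hour requirement without anyone having seen it met.

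Time to complete resolution, the other primary outcome, fares no better. A carried score of 1 or less creates an event that was not observed to last, and a carried high score supplies no event time.

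Most is at stake in the non-inferiority comparison, where anything that makes the two active arms look more alike favours the claim. Against placebo, similar crediting in both arms costs some power but does not produce a false claim.

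**Working it through.** **1. The plan's own figures.** Sample size calculation gives 91% relief, a 10-point difference, one-sided alpha 0.05 and beta 0.15. Reading the 10 points as the non-inferiority margin, n = (1.645 + 1.036)² × 2 × 0.91 × 0.09 / 0.10² = 117.8, so 118 per arm, as stated. For time to resolution (SD 2.2 days, 1 day, alpha 0.05, beta 0.10), n = 2 × [(1.645 + 1.282) × 2.2 / 1]² = 82.9, so 83 against the stated 84. The point concerns the analysis rules, not a wrong sample size.

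**2. The rules on three kinds of patient withdrawn for other medicine.**
- *Rescue for persistent pain, last score before rescue.* Entry requires a score of 5 or more, and a patient still in pain has a high last score. LOCF carries non-response. No harm to the relief rate.
- *Score has dipped, then other medicine is taken.* The rule also covers medicine for other symptoms, antibiotics and antivirals, so a patient whose throat score has recently fallen can be withdrawn. Carrying that score forward fills the remaining time and credits relief or resolution.
- *Score lowered by rescue.* This needs a diary score recorded after rescue and before withdrawal. The text neither establishes nor excludes one.

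Scores are taken three times a day, so a single low score cannot show a state lasting more than 24 hours. Only the carried values complete it.

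**3. Illustrative size.** The protocol gives no rescue rates or last scores, so the following are assumptions: true relief 91% (previous propellant, the planning value) and 81% (current propellant, exactly at the margin); one-sided alpha 0.05; unpooled standard error; and the same share c of non-responders credited in both arms. Then:

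- credited relief = p + (1 − p)c
- apparent difference d = 0.10 × (1 − c)
- chance of a false non-inferiority finding = Φ[(0.10 − d)/SE − 1.645]

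| c | Previous | Current | d | SE (n = 140) | False NI, n = 140 | False NI, n = 118 |
|---|---|---|---|---|---|---|
| 0 | 0.910 | 0.810 | 0.100 | 0.0410 | 5.0% | 5.0% |
| 5% | 0.9145 | 0.8195 | 0.095 | 0.0402 | 6.4% | 6.3% |
| 6.25% | 0.9156 | 0.8219 | 0.09375 | 0.0400 | 6.8% | 6.7% |
| 12.5% | 0.9213 | 0.8338 | 0.0875 | 0.0388 | 9.3% | 8.9% |

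Worked line for c = 5%, n = 140: (0.10 − 0.095)/0.0402 = 0.124, and Φ(0.124 − 1.645) = 0.064.

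A c of 12.5% would arise if a quarter of non-responders were withdrawn for other medicine and half of those credited. With 140 per arm that is 0.19 × 0.125 × 140 = 3.3 credited patients on the current propellant and 0.09 × 0.125 × 140 = 1.6 on the previous one.

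**4. Direction.** The increase depends on equal shares. At n = 140, if 5% of non-responders were credited in the previous-propellant arm only, d = 0.9145 − 0.81 = 0.1045, SE = 0.0407, and the rate is 4.0%. If they were credited in the current-propellant arm only, d = 0.91 − 0.8195 = 0.0905, SE = 0.0405, and the rate is 7.9%.

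**5. Against placebo.** Assuming 91% against 81%, n = 140 and one-sided 0.05, power = Φ(d/SE − 1.645): 79% at c = 0, 76% at c = 5%, 73% at c = 12.5%.

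**The case against.** The strongest reply is that a condensed article promises a full analysis plan before unmasking, and that the detailed working of LOCF on a duration-based endpoint belongs there. The endpoint definition itself demands more than 24 hours, so LOCF could be read as leaving that requirement intact. This stands in part: the analysis plan could still bar carried scores. But withdrawal and LOCF are choices this document makes, not gaps, and no later plan can recover diary scores that were never taken.

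Second, patients normally take rescue because they still hurt, and their last score is then high. This stands, and it keeps the expected effect small.

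Third, scores are taken before spraying, so a withdrawn patient who no longer sprays has no scheduled score. This also stands: a rescue-lowered score matters only if one falls between rescue and withdrawal. A reader might infer that rescue-lowered scores will routinely count as response; the text does not support that.

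Fourth, a reader might infer a large or one-directional bias towards non-inferiority. The documents do not support this either. The credited shares are assumed, and unequal shares could move the error rate either way.

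Fifth, efforts to obtain consent for data after discontinuation are planned, and patients are free to leave. Continued scoring can indeed only be requested, but the current text does not ask for it when other medicine is used. The per-protocol analysis presumably leaves these patients out, so it avoids the carried scores. It does so by dropping patients selected after randomisation, so it does not settle the matter.

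**Conclusion.** The point holds as a defect in the stated rules. Withdrawal from the study together with LOCF can turn a brief low score into a lasting response that was not observed, and LOCF does not yield a sound time to resolution. It does not show that the full-set result will be materially biased: size and direction are unknown, and a c of zero is possible. If equal shares of non-responders were credited in both active arms, with the truth at the 10-point margin and 140 per arm, the false non-inferiority rate would rise modestly, to 6.4% at 5% credited and 9.3% at 12.5%. The loss of power against placebo would be slight. The change should be made because it is cheap and the missing scores cannot be recovered later. Confidence is medium.

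**What to change.** **Withdrawal criteria; Concomitant treatments and forbidden medication.** Use of other medicine stops study medication only. With the patient's agreement, thrice-daily diary scoring continues to day 5 at the same times of day. Extend the existing effort to collect outcomes after discontinuation to these patients.

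**Statistical analysis.** Replace LOCF for the primary outcomes:
- No carried score may meet the 24-hour requirement.
- In every arm, medicine able to relieve sore throat, or an antibiotic or antiviral for the pharyngitis, taken before confirmed relief or resolution counts as not relieved or not resolved. Time to resolution is then censored at day 5. For medicine that cannot relieve sore throat, use the observed scores.
- Analyse observed scores regardless of rescue as a sensitivity analysis.
- Report non-inferiority in both the full and per-protocol sets, as already planned. Making one of them primary is a trade-off that this point does not settle.

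**Cost.** An amendment, which needs ethics committee approval, and a few more diary days for the patients concerned. Trial status says recruitment was still being prepared at submission. Relief rates may come out slightly lower, with slightly less power at the planned size. For example, with equal true rates, a 10-point margin, one-sided 0.05 and 140 per arm, power = Φ[0.10/√(2p(1 − p)/140) − 1.645], which is 89.9% at p = 91% and 84.8% at p = 89%.
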